# Efficacy of low-load resistance training combined with blood flow restriction vs. high-load resistance training on sarcopenia among community-dwelling older Chinese people: study protocol for a 3-arm randomized controlled trial

**DOI:** 10.1186/s13063-021-05495-z

**Published:** 2021-08-04

**Keywords:** Sarcopenia, Resistance training, Blood flow restriction

## Abstract

**Background:**

Sarcopenia is accompanied by a decline in muscle mass, muscle strength, and muscle function. Resistance training is the most potential training method for the prevention and treatment of sarcopenia. However, the conventional high-load resistance training (CRT) recommended by the American College of Sports Medicine is a challenge for older people with sarcopenia. As a novel training method, low-load resistance training combined with blood flow restriction (LRT-BFR) may elicit similar muscle mass and muscle strength gains as CRT but with less effort. The objectives of this study are to assess and compare the efficacy and safety of 12-week LRT-BFR and CRT on muscle strength, muscle performance, body composition, pulmonary function, blood biomarkers, CVD risk factors, and quality of life in community-dwelling older Chinese people with sarcopenia.

**Method:**

This is a 12-week, assessor-blinded, 3-arm randomized controlled trial with a non-exercise control group. Community-dwelling people over 65 years will be screened for sarcopenia according to the diagnostic criteria of the Asian Working Group for Sarcopenia (AWGS). Fifty-one subjects will be randomized into a LRT-BFR group (*n* = 17), a CRT group (*n* = 17), and a no-strength training control group (*n* = 17). The primary outcome is lower limb muscle strength. The secondary outcomes are body composition, upper limb muscle strength, pulmonary function, blood biomarkers, CVD risk factors, and quality of life. Post-intervention follow-up will be performed for 12 weeks. These indicators will be assessed at baseline (0 week), after the 12-week intervention (12 weeks), and at follow-up (24 weeks). The adverse events will also be reported. Data will be analyzed for all participants in an intent-to-treat plan.

**Discussion:**

This study is the first RCT that will systematically measure and compare the efficacy and safety of LRT-BFR and CRT in older people with sarcopenia on muscle strength, body composition, pulmonary function, blood biomarkers (inflammatory biomarkers, hormone, and growth factors), CVD risk factors, and quality of life. This study can provide an efficient and safe method to prevent the progression of sarcopenia in older people.

**Trial registration:**

Chinese Clinical Trial Registry ChiCTR2100042803. Registered on 28 January 2021.

**Supplementary Information:**

The online version contains supplementary material available at 10.1186/s13063-021-05495-z.

## Background

Sarcopenia is a condition characterized by a progressive decline in skeletal muscle mass, muscle strength, and physical performance associated with advancing age [1]. In 2017, the Asian Working Group for Sarcopenia (AWGS) reported that the prevalence of sarcopenia in persons aged ≥ 40 years ranged from 5.5 to 25.7% in Asian countries [1]. This is consistent with a prevalence of sarcopenia of 18.5% reported by Hu et al. [2] in 607 Chinese community-dwelling older people aged 60–90 years. Sarcopenia is concerning as it causes negative health outcomes to include falls, fractures, physical disabilities, decreased quality of life, and increased premature mortality [3]. As pharmaceutical treatments for sarcopenia are largely ineffective [4], these outcomes increase healthcare costs and bring a heavy economic burden to individuals and societies [5].

Sarcopenia results from complex and interdependent pathophysiological mechanisms. It involves not only muscle tissue loss and muscle contractile dysfunction, but also endocrine and metabolic abnormalities and is related to a low-inflammatory state referred to as inflamm-aging [6]. The mechanisms of sarcopenia are generally unknown; however, changes in specific biomarkers are speculated that characterize the condition. The most common biomarkers are inflammatory biomarkers (such as interleukin-6 [IL-6], tumor necrosis factor alpha [TNF-α], and serum C-reactive protein [CRP]), hormone (such as growth hormone [GH] and insulin-like growth factor 1 [IGF-1]), and growth factors (such as myostatin [MSTN] and follistatin [FST]).

Previous studies have shown that exercise (especially resistance training) is the most effective non-pharmacological intervention for increasing muscle mass and muscle strength. It also preserves muscle performance throughout the aging process [7–9]. To elicit muscle hypertrophy and muscle strength gains, the American College of Sports Medicine (ACSM) suggests older people engage in high-load resistance training programs (60–80% of one-repetition maximum [1RM]) for 2–3 days per week [7]. In addition, a meta-analysis evaluating strength training studies in older people has demonstrated that the effects of low-load resistance training (≤ 60% 1RM) on increasing muscle strength are less effective than those of high-load resistance training (≥ 60% 1RM) [10]. However, high-load resistance training is often perceived as being too difficult and technique-intensive for older people in clinical settings [11], especially frail people with sarcopenia. In addition, high-load resistance training can produce high mechanical stress on joints which may increase the risk of injury in older people [12]. Not researchers agree that high-load resistance training poses a risk for older adults [13, 14]. Nevertheless, in an epidemiological study, Kerr et al. [15] reported that over 90% of strength training injuries in people presenting to emergency departments between 1990 and 2007 were associated with high-load resistance training. Furthermore, the incidence of injuries was positively associated with the decrease in age-associated muscle strength, especially in women. In addition, musculoskeletal disorders in the aging population (such as osteoarthritis, gout, back pain) can decrease muscle strength and/or joint stability, leading to an inability to safely perform heavy load training [16]. Therefore, it is important to find a safe and feasible training method to increase muscle mass and muscle strength and avoid the risk of injury in older people with sarcopenia.

Low-load resistance training (LRT) combined with blood flow restriction (BFR) is a method of stimulating muscle growth by exerting external pressure on the proximal limbs through a compression device, such as a tourniquet or an inflatable cuff, that occludes venous blood flow during resistance training [17, 18]. Recently, several studies have demonstrated that low-load resistance training (20–30% 1RM) combined with BFR (LRT-BFR) may produce the same gains on muscle hypertrophy and muscle strength as observed with conventional high-load resistance training (CRT) [19, 20]. The studies also have demonstrated that LRT-BFR can increase muscle strength in lower [21] and upper limbs [22]; increase muscle size to include muscle cross-sectional area [CSA] [23], muscle thickness, and muscle mass [21, 22]; improve muscle performance evaluated by the timed up and go [TUG] test [23, 24]; decrease fat CSA [21]; and improve quality of life as reported by the 36-item Short-Form Health Survey [SF-36] [23] in older people. Moreover, LRT-BFR may make it easier for novice weight trainers to complete resistance training programs as LRT-BFR does not cause high joint force, subsequently reducing the risks of injury associated with CRT [25].

LRT-BFR may be an alternative resistance training method for healthy older people who are frail, have sarcopenia, or are unable to perform CRT. But some studies indicated that sarcopenia is a correlated risk factor for hyperlipidemia and insulin resistance, which is highly correlated with the risk of cardiovascular disease (CVD) [26]. A cohort with an average follow-up of 11.3 years demonstrated that sarcopenia is associated with higher CVD mortality [27]. Many studies have highlighted the lack of evidence relatively the cardiovascular safety of LRT-BFR particularly in older people at a high risk of CVD [28]. Due to the concerns about LRT-BFR in older people with cardiovascular disease, the efficacy and safety of LRT-BFR in older people diagnosed with sarcopenia should be carefully monitored. Little is known about changes in sarcopenia biomarkers following resistance training in people with sarcopenia. If LRT-BFR is to become a widely used training method for the management of sarcopenia, it is necessary to understand the physiological plus clinical impacts and the potential for cardiovascular adverse outcomes which may result from LRT-BFR training.

As CRT is currently the conventional method to increase muscle strength, size, and performance in older people, it is important to compare the efficacy and safety of LRT-BFR with CRT and a non-exercise comparison group in older people with sarcopenia. Thus, the main aim of this study is to assess and compare the efficacy and safety of two different resistance training interventions (LRT-BFR vs. CRT) with a non-exercising control group on sarcopenia. Thus, the objectives of this study are to (1) systematically evaluate the efficacy of 12-week LRT-BFR and CRT on lower body muscle strength (primary outcome), body composition, muscle performance, pulmonary function, blood biomarkers, CVD risk factors, and quality of life (secondary outcomes) and (2) compare the efficacy and safety between LRT-BFR and CRT, LRT-BFR and CRT, and CRT and no-strength training group, to provide an effective and safe method for the management of sarcopenia.

## Methods

### Study setting

This is an assessor-blinded, 3-arm, randomized intervention-control trial. Older people from four communities in the Chongming District of Shanghai, China, will be screened for the inclusion and exclusion criteria. A total of 51 older people meeting eligibility criteria will be enrolled in the study and randomized into one of three groups (17 in each group): a low-load resistance training with BFR group (LRT-BFR), a conventional high-load resistance training (CRT) group, or an education control group. Baseline, endpoint trial, and follow-up assessments will be conducted. The experimental flow chart is shown in Fig. 1. The Standard Protocol Items: Recommendations for Interventional Trials (SPIRIT) 2013 checklist is shown in Additional file 1. This study will be conducted in March 2021 at Xinhua Hospital Chongming Branch. The enrolment process, intervention, and assessments are presented in Table 1.

**Fig. 1 Fig1:**
[figure not shown]
The experimental flow chart showing the patient recruitment, intervention and assessment process

**Table 1 Tab1:** Schedule of enrolment, interventions, and assessments

Period	Screening	Allocation	Intervention period		Close-out	Follow-up
Time point	0 week	0 week	0 week	1–12 weeks	13 weeks	24 weeks
Inclusion and exclusion criteria	X					
Demographic data	X					
Informed consent	X					
Allocation		X				
LRT-BFR group				X		
CRT group				X		
Control group				X		
Body composition			X		X	X
Muscle strength			X		X	X
Muscle performance			X		X	X
Pulmonary function			X		X	X
Blood biomarkers			X		X	X
CVD risk factors			X		X	X
SF-36			X		X	X
Nutritional intake			X	X	X	X
Patient compliance				X	X	X
Dropout reasons				X	X	X
Adverse events				X	X	X

*CVD* Cardiovascular disease, *SF-36* 36-item Short-Form Health Survey, *LRT-BFR* Low-load resistance training with blood flow restriction, *CRT* Conventional high-load resistance training

### Inclusion criteria

Older people aged ≥ 65 yearsSarcopenia is diagnosed according to the criteria proposed by the AWGS. Sarcopenia is defined by ASMI < 7 kg/m^2^ for male and < 5.7 kg/m^2^ for female, using a bioelectrical impedance analyzer; 6-m walk (< 1 m/s); and/or handgrip strength (HG, < 28 kg for male and < 18 kg for female)Participants with physical disabilities (such as loss of hands, foot, or limbs) or suffering from dyskinesia disease who are unable to perform measurements and resistance training programParticipants with cognitive impairment, dementia, or severe mental illnessNot engaging in an exercise program or receiving exercise guidance (especially resistance training)

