### Recruitment

Subjects will be recruited using three approaches: (1) the annual community physical examination in four communities in the Chongming District, (2) educational lectures and talks about sarcopenia at community centers, and (3) home visits in cooperation with community workers to check on the health of home-dwelling older people who do not participate in community activities regularly. The subjects will be screened on site by SARC-F, a valid screening tool for sarcopenia in Chinese older people [29] that assesses 5 components: strength, assistance in walking, rising from a chair, climbing stairs, and falls. The questionnaire has a score range from 0 (the best) to 10 (the worst) with a SARC-F score ≥ 4 points diagnosed as having a risk of sarcopenia. Subjects with a SARC-F score ≥ 4 points will complete the AWGS screening consisting of assessment of appendicular skeletal muscle mass index (ASMI) with a portable bioelectrical impedance analyzer system (Inbody, S10, Korean); handgrip strength with a hand dynamometer (HK-6000, Hengkang, China); and a 6-m walk to determine walking speed. A physician will conduct the examination and consultation on subjects who meet the inclusion criteria, and excludes subjects who meet the exclusion criteria.

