### Randomization and blinding

Participants who meet the inclusion criteria and do not meet the exclusion criteria will be informed about the purpose and procedures of the study, what it will involve for them, and any risks involved in taking part as well as how to obtain more information about the study, low- and high-load resistance training and sarcopenia. After informed consent is obtained, subjects will be randomized into one of three groups: LRT-BFR, CRT, or control at 1:1:1 ratio. The randomization sequence, stratified by sex and age, will be generated and stored by a statistician who is not participating in the intervention and evaluation of the study, using SPSS version 20 statistical package (SPSS, Inc., USA). The random numbers and grouping assignments will be delivered in an encrypted electronic file to a research staff from another research for keeping this information. The therapists of this study will check the file and perform the intervention according to the grouping assignments. Except for therapists, all other participating staff, including the statistician, outcome assessors, and data managers will be blinded to the group assignment.

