### Interventions

#### Group protocols

Before the group protocols begin, all subjects will complete a one-repetition maximum (1RM) strength test to assess their muscle strength and to determine the intensity for resistance training in training groups. In addition, they will complete three pre-intervention lessons with the resistance training exercises to familiarize themselves with the training sessions. Subjects randomized to the control group will receive health education sessions only. The researchers will record the attendance of each participant in each training session. And if a participant misses a scheduled training session, the session will be completed within the training week.

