### Sample size

The sample size was calculated with PASS (version 11.0). According to a previous study, lower limb muscle strength is the most relevant outcome to show the efficacy of blood flow restriction. Thus, it was used as the primary outcome for calculating sample size [43, 44]. According to the data used in the study by Brandner et al. [44], the expected mean changes in lower limb muscle strength were approximately 11% for the BFR training group, 16% for high-load resistance training, and 0% for the control group with a pooled standard deviation of 13%. This sets the estimated total sample size at 42 subjects (14 in each group) to meet 80% power and an alpha of 0.05. Considering the frailty of some older people with sarcopenia, up to a 20% dropout rate is expected. Therefore, the sample size is set at 51 subjects (17 in each group).

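### Two evident exclusion conditions stand un-negated in the inclusion list and are missing from the exclusion list, so the written eligibility rule contradicts the trial's own procedures

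*Protocol article*

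**What the plan says.** The Inclusion criteria give, in order, an age limit, the AWGS definition of sarcopenia, a physical-disability item, a cognition and mental-illness item, and an item on not currently exercising. The physical item names people with limb loss and those "suffering from dyskinesia disease who are unable to perform measurements and resistance training". The next item names impaired cognition, dementia and serious psychiatric illness. Neither carries a negation.

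The Exclusion criteria cover five areas: thrombosis or clotting disorders; blood pressure and cholesterol; a history of stroke and of several cardiac, vascular, pulmonary and musculoskeletal conditions; dual antiplatelet agents; and anticoagulants.

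Two later sections say how the lists are used. Under Recruitment: "A physician will conduct the examination and consultation on subjects who meet the inclusion criteria, and excludes subjects who meet the exclusion criteria". The section on randomisation takes forward "Participants who meet the inclusion criteria and do not meet the exclusion criteria"; an explanation of the trial, consent and randomisation follow.

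**The concern.** Eligibility criteria define the trial population. Here two conditions that would ordinarily keep a person out are written as conditions for getting in, and no other list removes them. A screener who follows the text has no stated ground to turn away a person with dementia, or one who cannot perform the strength test.

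The procedures depend on people who can do these things. The 1RM test sets training intensity, and the primary outcome is an effort-dependent estimated 1RM of knee extension. The SF-36 is completed by the participant, and cuff pressure in the LRT-BFR arm is adjusted to the participant's own comfort, which presumes reliable self-report. If someone unable to perform the test were randomised, the primary outcome would be missing for a reason tied to their strength or function. That sits poorly with the missing-at-random assumption in Statistical analysis. Readers, ethics reviewers and anyone repeating the trial would also have the wrong description of who was studied.

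**Working it through.** No figure is in dispute, so the check sets the sections side by side.

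**Step 1. Is it a displaced heading?** The two items come after the age and sarcopenia criteria and before the item on not exercising, which is a genuine inclusion condition. The exclusion heading starts only after that. Moving the heading up would turn the exercise item into an exclusion, so a displaced heading does not explain the text.

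**Step 2. Can a negation be read in?** The exercise item carries its own *Not*. The list therefore negates explicitly where it means to, and nothing in its heading or layout supplies a negation for the two items before it.

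**Step 3. Does the exclusion list cover the same people?**

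| Condition in the inclusion list | Nearest entry in the exclusion list | Covered? |
|---|---|---|
| Limb loss, dyskinesia, inability to be measured or trained | History of stroke; musculoskeletal problems | In part |
| Impaired cognition, dementia, serious psychiatric illness | History of stroke, for a few people at most | No |

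**Step 4. What does the stated rule give?** The rule is: eligible = meets inclusion and does not meet exclusion. The two items can be taken in three ways.

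- Every inclusion item must be met: each participant must be unable to train and be cognitively or mentally impaired. The trial could not run.
- The two items are permissive: such people may enter.
- The two items carry a silent negation: such people are kept out. This is almost certainly what was meant, but it is not what is written.

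**Step 5. Which of these agrees with the rest of the protocol?**

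- Group protocols: "all subjects will complete a one-repetition maximum (1RM) strength test".
- Resistance training program: both training arms do elbow and leg exercises three times a week for 12 weeks.
- Muscle strength in the lower limb: the primary outcome needs repeated knee extensions against a weight.
- Health-related quality of life: the SF-36 is filled in by the participant.

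Only the third way is compatible with all four. The first two, which are the ones the words allow, contradict them.

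**The case against.** The strongest reply is that nobody would apply the list literally. Before inclusion a person completes SARC-F, handgrip, a 6-m walk and bioimpedance, so someone who cannot be measured would have difficulty reaching eligibility. A physician then examines each candidate, and the text does not say that the physician may remove people only on the listed grounds. Consent follows an explanation of purpose, procedures and risks, which is a practical barrier for people with marked cognitive impairment. The stroke and musculoskeletal exclusions take out part of the physical-disability group.

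Most of this stands, and it limits the point. It does not remove it. Handgrip and walking do not show that a person can do the knee-extension test or the band exercises. Consent is not a cognition criterion, and milder impairment or mental illness could pass. No section states the condition that was evidently intended.

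Three stronger readings are tempting and not supported:

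- *That the trial set out to enrol, or did enrol, people who cannot be trained.* The required 1RM test and supervised training speak against any such intention, and the article reports no enrolled participants.
- *That such a person would at once be lost after randomisation.* Group protocols place the 1RM test before the group protocols begin, while Table 1 puts screening, allocation and baseline assessment all at week 0. The column order suggests that allocation comes first, but the text does not fix it.
- *That the gap between 17 randomised and 14 required per group measures the damage.* That would rest on a supposed number of such entrants, which the documents do not give.

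**Conclusion.** The point holds as an error in the stated eligibility rule. Two evident exclusion conditions are placed, un-negated, among the inclusion criteria and do not appear among the exclusion criteria. The result contradicts Group protocols, Resistance training program, the primary outcome and the SF-36 section. It is most likely a list-placement slip. It still matters more than a slip in background text, because the rule yields the wrong population if followed.

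Its size cannot be put in numbers: the prevalence of these conditions among those screened is not given. The conclusion rests only on the wording of the two lists and of the sections that apply them. It does not assume that screening staff followed the text literally, and it does not put the sample size or power in question.

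**What to change.** Reconcile the two lists. Either move the physical-inability item and the cognition and mental-illness item to the Exclusion criteria, or keep them in place with an explicit negation; both serve equally well. Make the same correction in the ethics and registry records wherever they carry this wording. The Ethics approval and Dissemination sections already provide that route for protocol changes.

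Rewording alone may come too late to guide screening. Trial status says that recruitment began on 1 May 2021 and was expected to end around June 2021, and the article is dated 4 August 2021. The sponsor should therefore also state which criteria screening staff actually applied and report any participant enrolled with one of these conditions.

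The cost is a wording correction and a check of the screening records. No new procedure is needed, because Recruitment already provides a physician's examination.
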